### Participants

Participants are eligible if: they are community-dwelling aged 60 years or above and perceive their health as fair or poor. Screening on self-rated health will be performed through the first item of the SF-36 questionnaire: “In general, would you say your health is: (1) Excellent, (2) Very Good, (3) Good, (4) Fair or (5) Poor”.

Participants will be excluded if: they need help to go to the PCC; have cognitive impairment or diagnosed dementia; have a medical condition that contraindicates physical activity; have any severe mental health problem that hinders participation in a group dynamic; have an end-of-life situation.

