### Primary outcome

The primary outcome of the study is self-perceived health and will be estimated through the first item of the SF-36 questionnaire considering good self-rated health if they answer (1) Excellent, (2) Very Good or (3) Good, and bad self-rated health if they answer (4) Fair or (5) Poor.

For an overview of primary and secondary outcomes, outcomes measures, instruments and assessments time points, see Table 2.

**Table 2 Tab2:** Overview of outcomes, outcome measures, instruments and assessments time points

Outcomes	Outcome (measures)	Instrument	Assessment time points
Personal information	Age, gender, living arrangement, civil status, place of birth, educational background, job, medical conditions	Primary care records Self-report	T_0_
	Changes in living arrangement and civil status		T_1_, T_2_
Primary outcomes	Health status	SF-12 EQ-5D visual analog scale	T_0_, T_1_, T_2_
Secondary outcomes	Quality of life	SF-12	T_0_, T_1_, T_2_
	Social capital	European Values Survey	T_0_, T_1_, T_2_
	Social support	Inventory of social resources in the elderly	T_0_, T_1_, T_2_
	Social participation	Loneliness Este II Scale-Subjective Social Participation Index	T_0_, T_1_, T_2_
	Care and self-care	Self-care semFYC survey Appraisal of Self-Care Agency Scale	T_0_, T_1_, T_2_
	Emotional well-being	Warwick-Edinburgh Mental Wellbeing Scale (WEMWBS)	T_0_, T_1_, T_2_
	Loneliness	Gierveld and De Jong scale Social support perception scale	T_0_, T_1_, T_2_
	Depression	Geriatric depression scale (GDS-5)	T_0_, T_1_, T_2_
	Physical activity	The International Physical Activity Questionnaire (IPAQ)	T_0_, T_1_, T_2_
	Health literacy	Health literacy scale (HLS-EU-16)	T_0_, T_1_, T_2_
	Medication consumption Use of social and health resources	Primary care records Self-report	T_0_, T_1_, T_2_

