#### Data analysis

Reporting of the results will follow the CONSORT guidelines for randomised controlled trials [33].

First of all, a descriptive analysis will be conducted to characterize the intervention and the control group regarding socio-demographic, health and psychosocial variables.

The efficacy analysis will assess changes in the primary and secondary outcomes between the baseline and 3 months assessments comparing study arms (experimental and control group) with mixed linear models with repeated measures. Linear models will be used to adjust for covariables of interest, specially to correct differences between arms in the baseline characteristics, if applicable.

A diagonal matrix design will be considered for the between-participants covariance matrices (covariance structure for random factors). The between-participants correlations induced by the group delivery of intervention will be taken into account in the models.

Further testing of the study hypotheses will be conducted through covariance analyses, including in the model relevant covariates (age, gender, educational and socioeconomic levels), and effect modifiers. Estimates of effect will be computed for planned subgroups on age, gender, educational and socioeconomic levels and will be interpreted with caution as exploratory rather than definitive results.

It will follow the intention-to-treat principle, thus including all randomized participants with a baseline assessment regardless of their permanence in the study or their loss to follow-up, withdrawal or drop-out. Furthermore, sensitivity analyses will be conducted. In the first place, a ‘per protocol’ analysis will comprise all participants with no protocol violations and complete data in the measurements of the primary variables at baseline, end of treatment and follow-up. In a second sensitivity analysis, primary variables with a substantial number of missing values (higher than 5%) will be imputed.

All statistical analyses will use two-sided tests of statistical significance; estimates of the size of treatment effects will be presented with confidence intervals and significance tests. Significance levels will be set to a 5% level, applying the Bonferroni correction to adjust for type I error criteria. All analyses will be performed with SPSS version 20.

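### The efficacy model directs covariate adjustment mainly at observed baseline differences between arms, instead of at a fixed prognostic set that includes fair versus poor health at entry

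*Protocol article*

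**What the plan says.** All the analysis text is in the Data analysis section of the protocol article.

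- **Efficacy analysis.** It will "assess changes in the primary and secondary outcomes between the baseline and 3 months assessments", comparing arms "with mixed linear models with repeated measures".
- **Covariates in that analysis.** Linear models are to adjust for covariates of interest, "specially to correct differences between arms in the baseline characteristics, if applicable". No covariate is named here, and no criterion for a difference is given.
- **Second set of analyses.** "Further testing of the study hypotheses will be conducted through covariance analyses, including in the model relevant covariates". Here four covariates are named: age, gender, educational level and socioeconomic level.

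Three other sections bear on the point.

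- **Randomisation and blinding:** allocation is central, concealed, in random blocks and stratified by PCC.
- **Participants:** entry requires an answer of fair or poor to the first SF-36 item.
- **Primary outcome:** the same item is cut in two, with "bad self-rated health if they answer (4) Fair or (5) Poor" and the other three answers counted as good.

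**The concern.** Under concealed randomisation a baseline difference between arms is a chance event. Whether it is visible says nothing about whether the variable predicts the outcome, and it is prediction that makes adjustment useful. A rule aimed at visible differences has two consequences. The form of the efficacy model is settled only after baseline data have been compared by arm. And a strong predictor that happens to look balanced may be left out, so its gain in precision is lost.

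The primary outcome makes this sharper. Everyone enters as fair or poor, and the outcome cut merges those two answers. The baseline value of the binary outcome is therefore one constant. The fair-versus-poor split does vary between participants and is a natural candidate predictor of reaching good at three months, but neither the efficacy model nor the further covariance analyses name it.

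At stake are the precision of the primary estimate and a reader's confidence that the model was not shaped by the data.

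**Working it through.** No figure in the plan depends on the covariate rule, so there is none to reproduce, and the planned 390 is not changed by this point. The plan's inputs are 390 randomised (195 per arm), 20% dropout, and eight personal characteristics in Table 2. Evaluable: 195 × 0.8 = 156 per arm, 312 in total. Everything marked assumed is not in the documents.

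**1. How often chance alone triggers the rule.** Assume k independent characteristics, each judged at p<0.05. The probability that at least one looks imbalanced is 1 − 0.95^k.

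| k | Probability |
|---|---|
| 4 | 18.5% |
| 8 (Table 2 personal items) | 33.7% |
| 12 | 46.0% |

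Correlated items, such as living arrangement and civil status, would lower these figures. Splitting medical conditions into several items would raise them.

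**2. What the baseline measurement contributes to the binary outcome.** Code good = 1 and bad = 0. Eligibility makes the baseline value 0 for every participant, apart from anyone whose answer shifts between screening and the baseline assessment. Change is then T1 − 0 = T1, so the arm difference in change equals the arm difference at T1. The baseline row in the repeated-measures model carries no prognostic information for this outcome.

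**3. What fair versus poor could contribute.** Let f be the share fair at entry, pF and pP the probabilities of good at T1 from fair and from poor, and p = f·pF + (1 − f)·pP. The share of outcome variance explained is

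R² = f(1 − f)(pF − pP)² / [p(1 − p)].

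Assumed case: f = 0.75, pF = 0.30, pP = 0.08.

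- p = 0.225 + 0.020 = 0.245
- R² = 0.1875 × 0.0484 / (0.245 × 0.755) = 0.009075 / 0.184975 = 4.9%

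Across four assumed scenarios R² ran from 2.1% to 6.6%. The equivalent number of extra evaluable participants is 312 × R²/(1 − R²), and the standard error falls by 1 − √(1 − R²).

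| R² | Equivalent participants | Fall in standard error |
|---|---|---|
| 2.1% | 6.7 | 1.1% |
| 4.9% | 16.1 | 2.5% |
| 6.6% | 22.0 | 3.4% |

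**4. Imbalance-chosen versus fixed adjustment.** Simulation, 4,000 runs, all inputs assumed except 156 per arm: eight independent covariates each correlated 0.2 with a continuous outcome, true effect 0.3 SD, imbalance judged at p<0.05.

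| Model | Power | SD of estimate | Type I error (no effect) |
|---|---|---|---|
| Unadjusted | 77% | 0.113 | 4.6% |
| Covariates chosen by imbalance | 78% | 0.107 | 3.7% |
| Same covariates, fixed in advance | 89% | 0.093 | 4.2% |

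The covariates jointly explain 8 × 0.2² = 32% of variance, which is generous, so the 11-point gap in power illustrates the direction and does not forecast this trial. The imbalance rule recovers almost none of the available gain and is slightly conservative. At correlation 0.3 its type I error was 3.2%.

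**5. Error if the analyst could choose between models.** For two tests of the same hypothesis, take the correlation as about √(1 − R²) and compute P(max|z| > 1.96). R² = 2.1% gives correlation 0.989 and 5.7%; R² = 4.9% gives 0.975 and 6.0%; R² = 6.6% gives 0.966 and 6.2%.

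**The case against.** The other side has four arguments.

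**The sentence is looser than a strict trigger.** A reader might infer that adjustment happens only if imbalance is seen. The text does not say that. It speaks of covariates of interest and makes baseline differences the emphasised reason, and the closing proviso may attach only to correcting those differences. This stands. What remains is that imbalance is the only reason stated for adjusting in this model, and that no covariate is named there.

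**Baseline is already in the model.** A reader might infer that the plan ignores the baseline outcome. It does not: T0 is a repeated measurement in an analysis of change. For continuous measures, including the EQ-5D visual analogue scale that Table 2 lists under primary outcomes, T0 carries information. For the dichotomised item it is constant, so the argument fails there.

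**The order of analyses is implied, and type I error is addressed.** A reader might infer that two competing primary results inflate the error rate. The article calls one analysis the efficacy analysis and the other further testing, which suggests a hierarchy, and it applies a Bonferroni correction, though without saying to which family of tests. Nothing permits choosing the better result, so the inflation in step 5 is conditional on a freedom that the plan does not grant.

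**Covariate lists belong in an analysis plan, which may exist.** This would answer a mere omission. Here the article states a principle, and an analysis plan that followed it would inherit the weakness. The absence of fair versus poor from the list would be a minor matter on its own; it is raised as part of the repair. In the plan's favour, four suitable covariates are already named without any balance condition ("including in the model relevant covariates (age, gender, educational and socioeconomic levels), and effect modifiers"), but for the further analyses only.

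**Conclusion.** The point holds in a limited form. The stated rule ties adjustment in the efficacy model mainly to observed baseline differences, so the model depends on chance features of the data, and precision is given up when a prognostic covariate looks balanced. For the binary primary outcome, baseline as a repeated measure adds nothing, and the level that does vary is not named as a covariate.

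The size is modest. Chance would trigger the rule in about a third of trials with eight independent characteristics judged at p<0.05. Fair versus poor alone is worth about 7 to 22 of 312 evaluable participants, given the assumed response rates; how strongly it predicts in this population is not known from the article. The full covariate set would gain more if the other covariates are prognostic, but the article gives no figure for them.

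No bias is shown, and no type I inflation should be claimed for the rule itself: followed as one fixed rule it came out slightly conservative. Error would exceed 5% (about 5.7% to 6.2% at the R² values used here) only if the analyst were free to choose between models.

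**What to change.** 1. Remove the clause that aims adjustment at observed differences between arms.
2. Before post-intervention data are seen, fix one primary model that adjusts for PCC (the stratification factor), fair versus poor at baseline, age, gender, education and socioeconomic level, whatever the observed balance.
3. State that this model carries the primary conclusion. Label the unadjusted result and the other covariance analyses as supportive.
4. Keep the baseline comparison of arms as description only, with no role in choosing covariates.

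The cost is a change of wording in the analysis plan or a dated amendment. The covariates are obtained at screening or baseline, and centre is known from randomisation. The Trial status section reports that nobody had completed the outcomes assessment when the article was submitted, so at that point the change could be made without knowledge of results. The sample size is unaffected.

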**Fig. 2 Fig2:**
[figure not shown]
Conceptual framework of the intervention

The intervention methodology will be participatory with the purpose to promote the empowerment among participants. Group dynamics are designed to promote mutual knowledge and support, trust among participants, exchange of personal experiences among peers and the acquisition of new knowledge related to health literacy and self-management in order to lead to behavioural changes in their daily life that are meaningful for them and that positively affect their health and wellbeing. Health and social care professionals (five nurses, two social workers and two general practitioners) with experience working in the PCC will be previously trained as group facilitators by the research team during a two-day workshop. The training is based on how to apply the intervention guide.

The intervention consists in 12 sessions that are held weekly for 2 h and facilitated in groups of 12 to-15 people. The programme will be delivered in publicly funded PCC and in different locations of the neighbourhood. Specifically, nine of the 12 sessions will be delivered in the centre, and three sessions consist on local trips and are delivered in: a public space where to practice physical activity (park or pedestrian paths), a supermarket or a market and a community asset that offers social activities that can be of interest to the participants.

The intervention guide sets up a frame for the facilitators to conduct the group dynamics following common principles specified in a decalogue and an homogenous structure, while considering participants’ experiences, values and expectations. For example, several activities conducted as a group are highly personalized such as goal setting to change a daily habit to feel better, bringing personal belongings to introduce themselves and making an imaginary gift to another participant. Within the participatory approach, the locations of the three local trips are chosen and agreed by the group based on previous sign posting and mapping of local community assets, thus allowing a tailoring to specific interests and preferences of each group, as well as to the local context.

One or two health or social care professionals from the PCC will be observers of the intervention. They will complete an observation log including quantitative and qualitative measures of implementation such as fidelity and adherence.

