### Outcomes

Assessments will be conducted by health or social care professionals from the PCC who are not involved with the intervention delivery or observation. All outcome assessors will receive training in interview skills and outcome measure administration by the PI prior to the start. Outcomes will be measured at the following time points: baseline (T_0_), after the intervention is completed (T_1_) and 9 months after the end of the intervention (T_2_).

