### Sample size

A sample size of 390 participants, randomised to the intervention or the control group of 195 participants, will be needed to detect a clinically relevant benefit in self-perceived health after 3-month intervention. Self-perceived health is dichotomized as good health (including excellent, very good and good) and poor health (including fair and poor). The clinically relevant change has been defined as a 10% increase in the prevalence of participants who consider their health as good. The sample size has been estimated on a statistical power of 80%, a significance level of 95%, and an estimated dropout rate of 20%. A prevalence of 20% of bad self-perceived health in the ESCA 2012 in socio-economic class IVa was considered [32]. The calculations were performed with the “ene 3.0” programme.

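### The per-protocol set for the 3-month comparison also requires 9-month data, so valid 3-month outcomes are dropped because of later loss to follow-up

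*Protocol article*

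**What the plan says.** Three statements in the protocol article bear on this.

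- **The comparison.** Data analysis: "The efficacy analysis will assess changes in the primary and secondary outcomes between the baseline and 3 months assessments comparing study arms". No separate 9-month efficacy comparison is described there.
- **The sizing.** Sample size: 390 participants, 195 per arm, are needed to "detect a clinically relevant benefit in self-perceived health after 3-month intervention", with an allowance of 20% for dropout.
- **The per-protocol set.** Data analysis, as the first of two sensitivity analyses: "all participants with no protocol violations and complete data in the measurements of the primary variables at baseline, end of treatment and follow-up".

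The Outcomes section fixes three visits: T0 at baseline, T1 when the intervention is completed, and T2 nine months later. Follow-up in the per-protocol definition is therefore T2. The main analysis is by intention to treat in everyone randomised with a baseline assessment. The second sensitivity analysis imputes primary variables with more than 5% missing.

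**The concern.** The contrast ends at T1, but membership of the set is decided partly at T2. Whether a person's 3-month outcome counts then depends on what happens to that person in the nine months after it was measured. The consequences are:

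- **Lost information.** A complete T0 and T1 record is discarded although nothing needed for the 3-month contrast is missing.
- **Possible selection.** If people lost after T1 differ in their T1 outcome from those who stay, and this operates differently in the two arms, the per-protocol difference moves away from the one that all T0 and T1 completers would give.

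Unequal loss is plausible here. According to the Control group section, controls are offered the programme when the study ends, whereas the intervention arm has already had it, so the incentive to stay until T2 is not the same. The article does not show which arm would lose more.

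At stake is how the sensitivity analysis is read. If it departs from the main result, the reader cannot tell whether the cause is protocol adherence or dropout after the endpoint.

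**Working it through.** **1. Which visits does the rule need, and which does the contrast need?**

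| | T0 | T1 | T2 |
|---|---|---|---|
| Efficacy comparison (Data analysis) | yes | yes | no |
| Outcome used for sizing (Sample size) | – | yes | no |
| Per-protocol set (Data analysis) | yes | yes | yes |

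The mismatch is in the T2 column. It follows from the wording alone and needs no assumption.

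**2. The plan's own figure.** The article gives no number for the per-protocol set, so the starting point is its 390 (195 per arm). For 20% versus 10%, 80% power and a one-sided 5% test, the pooled formula gives 157 per arm. Then 157/0.8 = 196.25, rounded up to 197, or 394 in total. The unpooled formula gives 155, then 155/0.8 = 193.75, rounded up to 194, or 388 in total. The 390 lies between these. A two-sided test gives 199, then 249 per arm, or 498. That discrepancy is a separate matter. Here 390 is taken as given.

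**3. Outcomes dropped.** Assumption A: all of the stated 20% dropout occurs by T1, leaving 390 × 0.8 = 312, or 156 per arm. The further loss from T1 to T2 is not in the article, so a range is assumed. Dropped = 312 × further loss. Power is two-sided at 5% for 20% versus 10%, with n per arm, by the pooled normal approximation: Φ{(0.10√n − 1.96√(2 × 0.15 × 0.85)) / √(0.2 × 0.8 + 0.1 × 0.9)}.

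| Further loss by T2 (assumed) | Valid 3-month outcomes dropped | Left per arm | Power |
|---|---|---|---|
| 0% | 0 | 156 | 0.70 |
| 5% | 15.6, about 16 | 148 | 0.68 |
| 10% | 31.2, about 31 | 140 | 0.65 |
| 20% | 62.4, about 62 | 125 | 0.60 |

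The first row is the set that needs T0 and T1 only. Exclusions for protocol violations are ignored throughout.

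Assumption B: the 20% already covers loss to T2. The T2-complete set is then 312, and the set needing only T0 and T1 is at least that large. Of the 390 − 312 = 78 lost, anywhere from 0 to 78 could have had a T1 value that the rule drops.

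**4. Bias.** In each arm, let d be the share of T1 completers lost by T2, and g the gap in the proportion with good health at T1 (those who stay minus those lost). Keeping only those who stay shifts that arm's proportion by d × g. The per-protocol difference therefore shifts by d(I)g(I) − d(C)g(C).

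- If loss is unrelated to outcome (g = 0 in both arms), the shift is zero.
- If d and g are the same in both arms, the shift is zero.
- If 15% are lost in the intervention arm and 5% in the control arm, with a 15-point gap in both (all assumed): 0.15 × 15 − 0.05 × 15 = 2.25 − 0.75 = +1.5 points. With the arms exchanged it is −1.5 points. The sample size target is a 10-point difference.

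**The case against.** The strongest defence is that this is a sensitivity analysis. In the intention-to-treat analysis, T1 values from people later lost remain in use, and the second sensitivity analysis deals with missing data by imputation. Primary outcomes are collected at T0, T1 and T2, the model is for repeated measures, and a single completer set across all planned visits is a common convention. The article does not say that the set serves only the 3-month contrast, and a fuller plan may refine it. Most of this stands and limits the severity. It does not remove the mismatch: the rule is stated rather than left open, and the only efficacy contrast to which the article ties it is the 3-month one.

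Two stronger readings are tempting and are not supported.

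- **Selection on attendance.** A reader might infer that "all participants with no protocol violations" removes poor attenders, and so removes people from the intervention arm alone, because usual-care controls have no sessions to miss. The article never makes missed sessions a violation. Adherence appears only as an implementation measure: of the observers, the Experimental group section says "They will complete an observation log including quantitative and qualitative measures of implementation such as fidelity and adherence", and Process evaluation uses it in the same way. What counts as a violation may be defined in a full protocol or analysis plan that is not shown. Any bias figure for an attendance rule would quantify a rule that nobody has written.
- **A bias in favour of the programme.** A reader might infer that the set flatters the intervention. Nothing in the article indicates which arm would lose more people after T1, or whether those lost would be in better or worse health. The direction is unknown.

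**Conclusion.** The concern holds in a narrow form. The per-protocol set conditions a T0-to-T1 comparison on data from T2. That part rests on the article's wording alone.

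Its size rests on assumptions. If the 20% dropout is complete by T1 and a further 5% to 20% are lost by T2, about 16 to 62 of 312 valid 3-month outcomes are discarded, and power within this set falls from 0.70 to between 0.68 and 0.60. Any bias may go either way. It was 1.5 points in an example that needed threefold unequal loss and a 15-point outcome gap, and it is zero if loss is unrelated to outcome, or if both the loss and its relation to outcome are the same in the two arms.

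Severity is minor: the trial's main conclusion comes from the intention-to-treat analysis and does not depend on this set.

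**What to change.** Define the 3-month per-protocol set by complete primary-variable data at T0 and T1. Require T2 data only in a separate set for a 9-month analysis, if one is made. The condition on protocol violations can stay as it is.

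The change takes a sentence or two in Data analysis and no new data. Trial status reports that no participant had completed the outcomes assessment when the article was submitted, so at that point the change could have been made before any results were known. The one drawback is that the 3-month and 9-month per-protocol sets will differ in size, so both counts should be reported.

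### The protocol fixes single-step Bonferroni; Holm's step-down gives the same error control and never rejects less, so it is a cheap optional improvement

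*Protocol article*

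**What the plan says.** The Data analysis section of the protocol article contains one sentence on multiplicity: "Significance levels will be set to a 5% level, applying the Bonferroni correction to adjust for type I error criteria". It gives no number of tests, no adjusted level and no list of the hypotheses covered.

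Nearby text sets the frame. Testing is two-sided: "All statistical analyses will use two-sided tests of statistical significance". Intervals are promised: "estimates of the size of treatment effects will be presented with confidence intervals and significance tests". The article does not say whether those intervals will be adjusted for multiplicity. The efficacy analysis compares the arms on both primary and secondary outcomes from baseline to 3 months, and the subgroup estimates are described as exploratory.

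Table 2 ("Overview of outcomes, outcome measures, instruments and assessments time points") lists two instruments against the primary outcome and, by count, 11 secondary outcome rows: quality of life, social capital, social support, social participation, self-care, emotional well-being, loneliness, depression, physical activity, health literacy, and medication with resource use. The Sample size section makes no allowance for multiple testing.

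**The concern.** Single-step Bonferroni tests every hypothesis in a family of m at 0.05/m, however many of the others have already been rejected. Holm's procedure relaxes the threshold after each rejection without weakening the error guarantee. Where p-values are the basis for inference, Bonferroni therefore has no advantage in power over Holm.

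This could matter here because the programme is meant to move several related outcomes together. The Background section expects social capital, self-care and health literacy to reinforce one another, and the secondary objectives in the rationale list many such targets. A step-down procedure helps most when several effects in a family are real. If the correction runs across those outcomes, some real effects might be reported as non-significant when an equally valid procedure, applied to the same p-values, would have detected them.

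**Working it through.** **Figures in the plan.** The article gives no adjusted level, number of tests or power for secondary outcomes, so there is no stated figure on this point to reproduce. The one figure borrowed is the arm size ("A sample size of 390 participants, randomised to the intervention or the control group of 195 participants, will be needed"). With the stated 20% dropout, 195 × 0.8 = 156 per arm.

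**Both methods control the error.** Let m be the number of tests and m0 the number of true nulls.
- Bonferroni rejects when p ≤ 0.05/m. The family-wise error is at most m0 × 0.05/m ≤ 0.05, whatever the dependence. With independent tests and all nulls true it is 1 − (1 − 0.05/11)^11 = 0.0489 for 11 tests and 1 − (1 − 0.025)^2 = 0.0494 for 2.
- Holm orders the p-values and compares them in turn with 0.05/m, 0.05/(m − 1), …, 0.05, stopping at the first failure. The first true null to be rejected is reached by step m − m0 + 1 at the latest, so its threshold is at most 0.05/m0. The same inequality then bounds the error at m0 × 0.05/m0 = 0.05, with no added assumption.
- No Holm threshold is below 0.05/m, so every Bonferroni rejection is also a Holm rejection. The first Holm step is the Bonferroni test of the smallest p-value, so the chance of at least one rejection is identical.

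**Size if m = 11 (assumption).** The per-test level is 0.05/11 = 0.00455, critical value 2.84. An effect with 80% power at an unadjusted two-sided 5% has expected z of 1.96 + 0.84 = 2.80, so Bonferroni power is Φ(2.80 − 2.84), about 49%. With 90% unadjusted power, expected z is 3.24 and Bonferroni power is Φ(0.40), about 66%. Simulation (100,000 replicates per scenario, equicorrelated normal statistics, correlation 0, 0.3 and 0.5) gave this average power per true effect, Bonferroni to Holm:

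| Real effects of 11 | 80% unadjusted power | 90% unadjusted power |
|---|---|---|
| 1 | 48–49% to 48–49% (gain below 0.1 point) | 66% to 66% (below 0.1) |
| 5 | 49% to 51–52% (about 3 points) | 66% to 69% (about 3) |
| 11 | 49% to 59–60% (about 11 points) | 66% to 77–80% (12–15) |

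Holm rejected everything Bonferroni rejected in every replicate. With all nulls true its family-wise error was 0.038 to 0.050. With five real effects of 11 it was 0.032 to 0.040, against 0.023 to 0.027 for Bonferroni, so Holm uses error allowance that Bonferroni leaves unspent.

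**The same comparison in standardised differences.** A second simulation (200,000 replicates) assumed 156 independent participants per arm and correlation 0.3. For a difference of 0.3 SD, expected z = 0.3 × √(156/2) = 2.65, so Bonferroni power is Φ(2.65 − 2.84), about 42.5%.
- All 11 shift by 0.3 SD: 42.5% to 52.3%, that is 11 × 0.425 = 4.7 against 11 × 0.523 = 5.8 outcomes detected. At 0.4 SD: 75.7% to 87.6%.
- Five shift: 42.4% to 44.9% at 0.3 SD and 75.7% to 78.7% at 0.4 SD.
- Two shift by 0.3 SD: 42.6% to 43.1%.

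**Size if m = 2**, for example the two primary instruments (80% unadjusted power): about 71% to 71–72% with one real effect (gain at most about 0.2 point), and 71% to 76–78% with both real (5–6 points).

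**The case against.** The strongest reply is that nothing here is wrong. Bonferroni is valid and prespecified, controls the family-wise error strongly, and is contradicted nowhere in the article. Choosing between two valid procedures can be called a preference. It also suits a plan that promises intervals, because Bonferroni's simultaneous intervals match its tests directly and Holm has none as simple. All of this stands, and it is why the point is optional. It does not remove the advantage in testing, and the article does not commit to adjusted intervals.

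A reader might infer that power on the many secondary outcomes is being given away. The article does not support that. The sentence never says the correction spans the secondary outcomes; it could concern the two primary instruments, time points within the repeated-measures models, or subgroups. Eleven is also a count of table rows, not of tests: some rows list two instruments, and the last combines medication with resource use. An analysis plan that is not shown may settle the family, so leaving it unnamed in an article is not itself a fault.

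A reader might also take a gain of 10 points or more as the expected benefit. That requires every one of the 11 outcomes to respond, including physical activity and medication use, and the article gives no effect sizes for any of them. The second simulation also ignores the correlation from group delivery that the analysis section says will be modelled.

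**Conclusion.** The point holds as an optional efficiency improvement. Wherever the Bonferroni sentence covers two or more tests, Holm is at least as powerful for the same guarantee. That part rests on no assumption about family, correlation or effect size.

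The amount at stake cannot be derived from the article. If few secondary outcomes truly respond it is close to nil; it becomes material only if most of a large family responds. It therefore cannot be said that real effects will be missed, only that some may be. The validity of the planned tests is not in question.

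**What to change.** In the multiplicity sentence of the Data analysis section, replace the Bonferroni correction with the Holm–Bonferroni step-down procedure, applied to the same family of tests the sentence is meant to cover. The replacement should not be limited to the secondary outcomes, because any other tests now under the sentence would then have no stated correction. Report Holm-adjusted p-values beside 95% confidence intervals labelled as unadjusted.

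The change is one phrase and a sort of the p-values; sample size, data collection and participants are unaffected. According to Trial status, no participant had completed the outcomes assessment when the protocol was submitted, so a change at that stage would have come before any outcome results.

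There are two costs. Simultaneous intervals matching Holm are less simple than Bonferroni's, and an unadjusted interval may exclude zero beside a non-significant adjusted p-value, so the label on the intervals must be clear. If matching simultaneous intervals matter more to the investigators than the extra rejections, keeping Bonferroni is defensible.
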